##### Gather Patient and Carer Experiences

The focus shifts to patients with FMD and their caregivers, who share their experiences through 12 to 15 filmed narrative interviews. These narratives capture their journey and key emotional moments after the FMD diagnosis.

##### Trigger Film Creation

A 30-minute “trigger film” is edited from the narrative interviews, allowing staff to connect more deeply with the experience of patients with FMD by seeing and hearing their perspectives directly.

##### Joint Workshop

This workshop brings together staff, patients with FMD, and carers to review the film and share insights. It is a collaborative session essential for identifying specific constructs for applying XR technology in the FMD care process, spanning from clinic to home.

##### Small-Group Work on Identified XR Priorities for Defining XR Technology Application

Small groups are formed to address specific XR constructs, such as a virtual cognitive behavioral therapy coach, XR force feedback games, and XR position feedback games. They operate in 4-week Agile sprints to define and refine XR technology applications that align with the needs identified in the joint workshop.

##### Celebration and Face-Validating XR Technology Event

After specific prototype developments and design verification, a face-validation and celebration event takes place. This event celebrates progress and fosters a sense of achievement among participants.

##### Long-Term Impact

While each 4-week sprint provides incremental improvements, the co-design process over a maximum of 3 years, culminating in construct validation, is expected to lead to a patient-centered XR technology platform tailored to enhance FMD care from clinic to home settings for clinical usability and ecological validity testing.

#### Addressing Accessibility, Inclusivity, and Equity

The XR platform will include personalization and accessibility features, such as adjustable haptic controls, audio guidance, and customizable displays, tailored to patients’ needs as identified in the EBCD process. We aim for a diverse participant base, ensuring that the technology is suitable for patients across various ages, cultural backgrounds, and socioeconomic statuses. By actively recruiting underrepresented groups, especially female individuals, in whom FND is more prevalent [99], through patient advocates and charities, we prioritize inclusivity in development. Continuous feedback for prototyping and design verification, with parallel face validation, will allow iterative refinement based on user requirements.

#### Partnership and Stakeholder Involvement Strategy

Industry partners Nudge Reality Ltd and HumanRobotiX Ltd as well as robotic rehabilitation and haptic technology experts will enhance the platform with design-for-manufacture principles. Collaboration with FND charities and clinical networks will ensure that patient perspectives remain central. Patient advocates [name] and [name], from the EPSRC Network+ seed-funded project [35], will support outreach and participant recruitment.

#### Ensuring Responsible Innovation

The EBCD process will ensure transparency, inclusivity, and accountability by documenting development and integrating feedback, resulting in an accessible, ethical XR platform for FMD rehabilitation from clinic to home settings, aimed at enhancing both quality of life and health equity.

### Activity 2, Phase 2 (Mo 1-48): Requirement Translation of XR Technologies in FMD

#### Overview

To develop the XR platform for FMD rehabilitation from technology readiness level (TRL; a scale [ranging from 1 to 9] used to assess the maturity of a technology from concept [TRL 1] to full deployment [TRL 9]) 2.0 [35] to 3.5, we adopt a work cycle approach in work package 1, focusing on meeting user and stakeholder needs for translation and impact. Using coproduction, we ensure patient-centered quality by design (ISO 16355-1:2021) through patient and public involvement and engagement, iterative critical function validation (4-wk sprints), and testing (ISO 9241-220:2019) in an engineering laboratory with healthy participants. NVIDIA provides guardrails for physical AI through its Isaac platform and Jetson hardware, ensuring safe, reliable, and tested deployment of the XR platform. The work packages are illustrated in Figure 5 and are detailed in the Work Packages subsection, showing how quality function deployment (QFD; a structured method for translating user needs into engineering specifications during system development) will be operationalized alongside EBCD and 4-week Agile sprints during XR platform development.

**Figure 5 figure5:**
[figure not shown]
Overview of the work packages highlighting their structure, interactions, and key objectives within the project. TRL: technology readiness level.

#### EBCD Workshops: Capture of User Needs

EBCD workshops with patients, caregivers, and clinical staff will generate narrative data and structured feedback identifying key emotional touchpoints and rehabilitation needs. These are synthesized into user stories and functional requirements using thematic analysis in NVivo (Lumivero).

#### QFD Application: Translation Into Engineering Specifications

These user requirements are then mapped into a QFD matrix (house of quality) to prioritize technical features based on the frequency and criticality of patient and staff feedback. Relationships between user needs (eg, “easy-to-use interface” and “low visual discomfort”) and design components (eg, haptic resistance levels and XR visual rendering) are identified. Qualitative insights into quantifiable system parameters and performance metrics (eg, range of motion thresholds and feedback latency <100 ms) are translated. Each QFD matrix is reviewed by the cross-functional team (engineers, clinicians, and patient advocates) at the start of every sprint cycle, ensuring alignment between stakeholder input and design focus.

#### Agile Sprints: Implementation and Feedback Loops

Each 4-week Agile sprint consists of the following components:

Week 1: sprint planning meeting, informed by QFD-derived priorities and usability issues identified in prior sprint testingWeeks 2 and 3: iterative prototype refinement, integrating hardware (HRX-1, brain imaging, and neurostimulation if necessary) and software (XR environment)Week 4: sprint review and testing session with 3 to 5 participants (patients or controls), using the System Usability Scale (SUS; a standardized 10-item questionnaire used to evaluate the usability of a product or system) and open-ended feedback

#### Validation and Loop Closure

Usability feedback is again categorized thematically and translated back into the next iteration’s QFD matrix, closing the loop between user experience and technical refinement. This process ensures that the prototype evolves in a traceable, patient-centered, and evidence-driven manner.

#### Work Packages

##### Work Package 1: Advancing Prototype and Construct Validity Through TRL 2.0 to 3.5

###### Work Cycle 1a: Defining User Needs and Ensuring Face Validity

This cycle engages patients with FMD, carers, health care staff, and FND charities through surveys, focus groups, and workshops following the EBCD approach (Figure 4). Insights inform critical function analysis and QFD to align XR technology with stakeholder needs, achieving face validity through iterative 4-week sprints.

###### Work Cycle 1b: Prototype Development and Verification

The HRX-1 device is reengineered and integrated with the Meta Quest 3 headset and wearable brain imaging capabilities, guided by QFD. A prototype characteristics matrix informs iterative development and verification through 4-week sprints to ensure compliance with design requirements (Figure 6). Expectation maximization (EM) is used in conjunction with the Kalman filter [3] when model parameters (eg, transition probabilities and noise covariances) are unknown and must be estimated from data. While the Kalman filter excels at real-time state estimation, assuming fixed parameters, EM is ideal for parameter estimation in probabilistic models, especially when working with incomplete or noisy data, such as neural signals. In brain state transitions (Figure 1), EM is used in switching state-space models to learn hidden brain state dynamics (eg, attention states) from fNIRS and EEG recordings, while the Kalman filter performs the real-time estimation of latent states once the model is trained [3]. These methods will be combined with EM performing offline learning, with the Kalman filter embedded in its expectation step for state inference [3]. This approach is well documented in neuroscience and signal processing literature [100,101].

**Figure 6 figure6:**
[figure not shown]
Verification and validation (V&V) of the artificial intelligence– and machine learning–enabled extended reality platform. System-level verification will be conducted to identify design flaws and resolve requirements. ISO/IEC 5927:2024 provides safety and well-being guidelines for immersive technologies such as virtual reality and augmented reality, covering risks such as motion sickness, eyestrain, and safe setup practices. The ISO 9241 series focus on ergonomics and usability in human-system interaction, with portions such as 9241-920 and 9241-940 specifically addressing the design and evaluation of haptic and tactile feedback. Together, these standards support the development of user-friendly, safe, and effective extended reality (XR) systems. IEC: International Electrotechnical Commission; ISO: International Organization for Standardization.

For personalization, the XR platform will incorporate haptic device control algorithms that adapt both the difficulty of training tasks and the parameters of haptic feedback in real time [3]. Specifically, data streams from haptic device sensors (eg, motion and force input) and neuroimaging modalities (eg, fNIRS and EEG) will be used to infer user brain-behavior engagement, motor effort, and cognitive workload. A reinforcement learning framework will then adjust task parameters such as target accuracy thresholds, movement speed, or visual feedback gain based on performance trends and error profiles; for example, if a user demonstrates consistent overshooting or hesitation during reaching tasks, the system will gradually adjust the virtual target zones and reduce haptic resistance to facilitate motor learning while maintaining an appropriate level of challenge. Similarly, attention-aware modeling using switching state-space models will classify brain states associated with fatigue or disengagement, prompting breaks or switching to lower-load tasks. These adaptive control strategies will be trained offline using EM to learn individual response patterns and updated in deployment using embedded Kalman filtering for real-time state estimation [3]. This integration of AI and ML enables dynamic personalization of the rehabilitation experience, ensuring that the XR environment responds to each patient’s evolving abilities, optimizing both usability and therapeutic efficacy. At this stage, design-time guardrails must be established through trustworthy development pipelines that integrate third-party safety assessments (eg, MATLAB, Simulink, System Composer, and Requirements Toolbox) and follow robust processes focused on reliability and security in the AI- and ML-enabled model-based systems engineering of the XR platform.

###### Work Cycle 1c: Construct Validity Testing

SUS assessments and open-ended interviews will be conducted with healthy controls to refine sensor, effector, and AI and ML usability (Figure 6). Validation-time guardrails are enforced through hardware-in-the-loop high-fidelity simulation environments (eg, MATLAB, Simulink, System Composer, and Requirements Toolbox), enabling the testing of the AI- and ML-enabled XR platform across many real-world scenarios (eg, sensor fault [102], security, and authenticity [103]). Pilot studies will then assess convergent and divergent validity of brain responses (eg, beta oscillations and SMA efferent network activity from dFC) using the XR platform in an engineering laboratory environment.

##### Work Package 2: Advancing Usability, Validity, and Strategic Delivery

###### Workstream 2a: Clinical Usability and Ecological Validity Testing

Usability studies will be conducted with 50 patients with FMD for 3 alternate-day clinic visits, evaluating SUS scores and the platform’s clinical validity in a safe, controlled setting. Deployment-time guardrails will be responsible for executing real-time performance monitoring and error detection, as well as initiating fallback procedures during the XR platform operation under controlled clinical conditions.

###### Workstream 2b: Strategic Road Map for Development and Product Delivery

A translation and impact plan using the results from workstream 2a will be developed for future validation in a stepped care clinic-to-home framework (TRL ≥4.0). Guardrails for surveillance will ensure continuous monitoring, issue detection, regulatory compliance, and safe updates to maintain safety and performance. To support the scalability and real-world adoption of XR-based rehabilitation for functional limb weakness in FMD, this study will conduct a rigorous economic evaluation using the generalized risk-adjusted cost-effectiveness (GRACE; a method to adjust willingness-to-pay [WTP] thresholds by considering risk, severity, and outcome distributions) framework [97]. This approach improves upon traditional CEA by integrating patient-level risk preferences and variability in health outcomes, which are especially important in heterogeneous conditions such as FMD. A discrete choice experiment will be conducted with 50 patients diagnosed with functional limb weakness to estimate their WTP thresholds for home-based XR therapy and to quantify the quality-of-life impact of untreated symptoms. We will quantify the perceived impact of untreated FMD symptoms (functional limb weakness) on quality of life; estimate patients’ WTP thresholds for home-based XR rehabilitation; and identify trade-offs that patients are willing to make between convenience, effectiveness, risk, and cost. This will allow us to elicit patient-centered utility values and incorporate preference heterogeneity into the economic model. The results will inform a patient-centered utility model that accounts for preference heterogeneity. Unlike traditional CEA that relies on average quality-adjusted life years (QALYs), the GRACE framework computes generalized risk-adjusted QALYs, incorporating outcome variance (uncertainty in outcomes), skewness (asymmetric benefits), and kurtosis (extreme outcome tails) to better reflect patient-specific risk profiles and treatment uncertainty. This allows us to reflect not only the mean effectiveness of the XR intervention but also its distributional effects, including benefits for those at higher risk or with more severe impairment. This enables the calculation of a risk-adjusted WTP threshold (*K_GRACE_*) using the following formula:

*K_GRACE_* ≥ *ΔCost* / *Δ*(*GRAQALYs*)

where *ΔCost* is the incremental cost of the XR intervention compared to standard care, *GRAQALYs* stands for generalized risk-adjusted (for baseline severity, disability, and risk preferences) QALYs, and *Δ*(*GRAQALYs*) is the gain in risk-adjusted health benefits (QALYs). By integrating clinical outcomes, cost, and patient risk tolerance, this approach provides a robust basis for determining value for money, guiding pricing, reimbursement, and the equitable implementation of XR rehabilitation in FND care pathways. Ultimately, this integrated approach ensures that home-based XR rehabilitation is not only clinically promising but also economically justifiable and aligned with real-world patient values.

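### The planned economic evaluation claims value for money against standard care, but the study described has no source for an effect or a cost relative to standard care

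*Protocol article*

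**What the plan says.** Workstream 2b states that "this study will conduct a rigorous economic evaluation using the generalized risk-adjusted cost-effectiveness" framework. The decision rule compares a risk-adjusted willingness-to-pay threshold, K_GRACE, with ΔCost / Δ(GRAQALYs). ΔCost "is the incremental cost of the XR intervention compared to standard care", and Δ(GRAQALYs) "is the gain in risk-adjusted health benefits (QALYs"). The adjustment draws on the variance, skewness and kurtosis of outcomes, and is said to "reflect not only the mean effectiveness of the XR intervention but also its distributional effects".

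Two conclusions are attached in advance: that "this approach provides a robust basis for determining value for money", and that the approach makes certain that "home-based XR rehabilitation is not only clinically promising but also economically justifiable".

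On patient testing, Workstream 2a says: "Usability studies will be conducted with 50 patients with FMD for 3 alternate-day clinic visits, evaluating SUS scores", together with a clinical validity for which no measure is named. Workstream 2b adds a discrete choice experiment in 50 patients with functional limb weakness. The same workstream places clinic-to-home validation in future work at technology readiness level (TRL) 4.0 or above. The Discussion (Summary) says that full-scale efficacy has still to be shown.

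**The concern.** A cost-effectiveness ratio against standard care needs two contrasts: what XR costs beyond standard care, and what health it adds beyond standard care. The patient work described observes one group using the device in clinic and asks patients about preferences. Neither activity produces either contrast.

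Any ratio would therefore rest on effect and cost inputs from elsewhere, which the article does not identify. Yet the text presents the result as a basis for pricing and reimbursement, and the Discussion plans early engagement with commissioners and health technology assessment bodies. Those readers could take an assumption-driven ratio for evidence from this study. The wording also settles the answer beforehand, although an evaluation must be able to find that the device is not worth its cost.

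**Working it through.** The article gives no ΔCost, utility or QALY figure, so there is no ratio to reproduce. The check is to trace each term of K_GRACE ≥ ΔCost / Δ(GRAQALYs) to the data collection described.

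1. **K_GRACE (threshold side).** Needs willingness to pay and risk preferences. The choice experiment (Workstream 2b) elicits willingness to pay and trade-offs between convenience, effectiveness, risk and cost. A source is described.
2. **ΔCost against standard care.** Needs the cost of XR and of standard care. No collection of resource use or cost, and no external cost source, is described.
3. **Δ(GRAQALYs) against standard care.** Needs health with XR and with standard care over a stated period. Workstream 2a names the System Usability Scale (SUS), which measures usability, in one group. The roughly 15 healthy participants (Healthy Participants) serve usability and construct validity and are not a standard-care comparator. No source is described.
4. **Variance, skewness and kurtosis of outcomes.** These describe the distribution of the same health outcome, so they lack a source for the same reason as item 3.
5. **Reference state.** The choice experiment asks about the burden of untreated symptoms, whereas the formula compares with standard care. Even a good estimate of that burden is not the contrast required.

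**The sample size does not fill the gap.** The only power calculation (Patients With FMD) uses d = 0.81 for SUS between the position and force feedback tasks, two-sided α = .05 and 80% power, and states about 15 per group. A paired comparison reproduces this. The normal approximation is (1.960 + 0.842)² / 0.81² = 7.85 / 0.656 = 12.0, and the paired t-test gives 14.004, rounded up to 15. The figure concerns one XR task against another and says nothing about XR against standard care.

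**The article's own timetable agrees.** Work package 1 runs from TRL 2.0 to 3.5 (Activity 2, Overview), clinic-to-home validation comes at TRL 4.0 or above, and efficacy is still open. The evidence needed for items 2 to 4 belongs to a later stage than the conclusions drawn here.

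**The case against.** The strongest reply is that this is a model, not a trial-based analysis. Workstream 2b speaks of an economic model, and a model may take effects and costs from outside the study. An article may leave those sources, the time horizon and the outcome measures to a full protocol or health-economic plan. The workstream is framed as a road map, and the Discussion makes adoption conditional on efficacy being shown. All of this stands, and the absence of model detail is not the finding. It does not rescue the stated conclusions: an exploratory model built on outside assumptions cannot make certain that the device is economically justified.

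Several stronger readings are tempting but not supported:

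- **A reader might infer that no comparator is specified.** Standard care is named in the formula. What is missing is a source of data on it.
- **A reader might infer that the ratio cannot be estimated at all, or that QALY gains are limited to the few days of the visits.** Nothing restricts the model's horizon to those visits, and external inputs could yield an early estimate.
- **A reader might infer that SUS and the choice experiment are all the patient data.** Filmed narrative interviews, open-ended sprint feedback and portable brain imaging are also planned, though none of these is a QALY or a cost.
- **A reader might infer that the device is never used at home.** Participant Population and Textbox 1 refer to home-based XR, while Workstreams 2a and 2b describe clinic visits and future home validation. The text is inconsistent and does not settle the matter.
- **A reader might infer that 50 patients are too few to estimate skewness and kurtosis.** The article does not say these moments will be estimated from those patients.

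**Conclusion.** The concern holds as an overclaim. Of the two sides of the decision inequality, the threshold side has a described source. The ratio side has none for either of its terms, nor for the outcome distribution used in the risk adjustment. The value-for-money conclusion is therefore not supported by the design as described, and it is fixed before any result exists.

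No numerical size can be attached, because the article gives no cost or utility figure. The judgement assumes that the article's account of patient testing and economic data collection is substantially complete. If a fuller document names external effect and cost sources, an exploratory estimate becomes possible, but the two stated conclusions would still go too far. The usability aim is unaffected. The point should be corrected, but it does not threaten the study.

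**What to change.** - Relabel the analysis as an early, exploratory, model-based evaluation. One suitable form is a headroom calculation: for a positive gain, the inequality rearranges to ΔCost ≤ K_GRACE × Δ(GRAQALYs). With a threshold fixed beforehand, report the largest incremental cost that satisfies it over stated ranges of assumed QALY gain and duration.
- Use the choice-experiment results as inputs, and label every effect and cost input as external or assumed. Naming the sources and marking the analysis exploratory is the minimum; the headroom form is one option.
- Show the skewness and kurtosis adjustments as scenarios.
- Delete the claims "this approach provides a robust basis for determining value for money" and "home-based XR rehabilitation is not only clinically promising but also economically justifiable".
- Leave the ΔCost/ΔQALY estimate against standard care to the later study at TRL 4.0 or above.
- Reconcile the home-setting text in Participant Population and Textbox 1 with the clinic visits and deferred home validation in Workstreams 2a and 2b.

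The cost is redrafting, some work to document the model inputs, and a weaker economic claim. No additional patients are needed.
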